### Statistical analyses

The statistical analysis plan will be described in detail and published in “BMC Medical Research Methodology”.

Our primary analyses for all outcomes will be adjusted for the three stratification variables (number of previous births (0 or more), centres (Roskilde or Herlev), and previous larger pelvic surgery (yes/no)). Our secondary analysis for all outcomes will be adjusted for the three stratification variables (see above) and other prognostic variables (history of chronic pelvic pain (yes/no), co-morbidity, enlarging of the abdominal incision to remove uterus (yes/no), multiple adherences or need for other laparoscopic procedures (yes/no). Full analysis will be carried out on both groups, the intention-to-treat population (all randomized participants) and observed cases.

Longitudinal data will be analysed using area under the curve, continuous data will be analysed linear regression, dichotomous data will be analysed using logistic regression, and survival data will be analysed using cox regression. We will perform two sided statistical tests.

We will assess if the thresholds for statistical significance and clinical significance are crossed using the five-point procedure as suggested by Jakobsen et al. [14]. This procedure will include adjustments of thresholds for significance according to the number of primary outcomes (*P*-value threshold 0.033) and number of randomized participants. We will use a Bayes factor threshold for significance of 0.1 based on the prior anticipated intervention effect (see sample size calculation).

We will register if postoperative pathologic examination unexpectedly reveals cancer in a stage indicating further surgery, or if surgery must be converted to open surgery, for other reasons than to remove the uterus. However, we expect such cases to be rare and we will therefore include such participants in the primary analysis. Sensitivity analyses will be performed if the proportion of such cases is larger than expected.

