### Sample size calculation and power estimation

Because our trial is designed with two primary outcomes, our sample size calculation will be based on a type 1 error of 3.3% [15].

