#### Postoperative pain

We use a 100 mm VAS-score to assess pain. We consider 10 mm as the minimal relevant difference with a standard deviation of 20 mm and we accept a risk of type I error of 3,3% and a risk of type II error of 10%. This results in a sample size of 92 patients in each arm of the trial.

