#### SF 36 quality of life

We consider 4 points on the SF 36 quality of life as the minimal relevant difference with a standard deviation of 12 points and we accept a risk of type I error of 3.3% and a risk of type II error of 10%. This results in a sample size of 190 patients in each arm of the trial.

To be able to assess both of the co-primary outcomes, we therefore chose 2 × 190 participants as our necessary sample size.

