### Trial strengths and limitations

This trial has a number of strengths. First, the randomized design makes it possible to validly assess the effects of the two surgical interventions. Second, the trial has a high degree of external validity because we assess the effects of operative procedures as they are performed in most gynecological departments and we use two recruiting centers. Third, the risk of systematic errors is reduced by central randomization stratified for prognostic factors [16, 17], blinding is used to the highest possible extent, and data is analysed according to the intention-to-treat principle. Fourth, in trials investigating operative procedures it is often difficult to distinguish whether different effects of the operative techniques or varying skills of the surgeon cause a supposed difference. In this present trial the same experienced surgeons perform both the conventional and 3D operations. This, together with the overall low risk of bias of this trial, contributes to a high degree of internal validity. Finally, we estimated a sample size adjusted for two primary outcomes using realistic anticipated intervention effects and we performed power calculations for all secondary outcomes, and we planned to adjust the thresholds for significance if we do not reach the planned sample size. This limits the risks of random error [14].

A limitation of this trial is that we will probably not be able to detect a difference in complication rate between the 2 arms of the trial. The overall low complication rate following laparoscopic hysterectomy requires a large sample size to detect a possible difference. We expect it is more likely to demonstrate a difference in postoperative pain or quality of life, two other relevant clinical outcomes that have not previously been assessed following 3D laparoscopic hysterectomy.

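### Two primary outcomes each tested at 0.033 do not cap the overall p-value error at 5%, and 190 per arm gives 86.8% SF-36 power at that threshold, not the stated 90%

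*Protocol article*

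**What the plan says.** The protocol article names two primary outcomes: the SF-36 physical health score at 6 weeks and postoperative pain on a 100 mm scale.

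- **Threshold.** Under Statistical analyses: "This procedure will include adjustments of thresholds for significance according to the number of primary outcomes", with 0.033 given as the p-value threshold. Also: "We will perform two sided statistical tests". The same paragraph sets a Bayes factor threshold of 0.1, based on the anticipated effect.
- **Reason for 3.3%.** The section on sample size and power explains: "Because our trial is designed with two primary outcomes, our sample size calculation will be based on a type 1 error of 3.3" (per cent).
- **SF-36.** "We consider 4 points on the SF 36 quality of life as the minimal relevant difference with a standard deviation of 12 points"; "we accept a risk of type I error of 3.3% and a risk of type II error of 10" (per cent); "This results in a sample size of 190 patients in each arm of the trial".
- **Pain.** "We consider 10 mm as the minimal relevant difference with a standard deviation of 20 mm", with the same two error risks, giving 92 per arm. The larger figure, 190 per arm, is adopted.
- **Claimed benefit.** Trial strengths and limitations lists the sample size adjusted for two primary outcomes among several measures and concludes: "This limits the risks of random error".

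The article names no step-down or hierarchical rule, no overall error level for the two primary outcomes, and no correlation between them.

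**The concern.** Lowering the threshold because there are two primary outcomes makes sense only if either outcome can carry a positive claim. If both had to be significant, no reduction would be needed. The error that matters is then a false claim on at least one of the two. The threshold 0.033 is close to 0.05/1.5 = 0.0333. It therefore lies between no adjustment (0.05) and a full Bonferroni split (0.05/2 = 0.025), and it corrects only in part.

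The threshold also sets the sample size. If 190 per arm does not follow from 0.033, the trial has less power for the SF-36 than the article says, and the SF-36 is the outcome that determines its size.

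Two things are at stake: what a reader may conclude from one significant primary outcome, and whether the stated 90% power is true.

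**Working it through.** **Inputs** (protocol article): SF-36 difference 4, SD 12; pain difference 10 mm, SD 20 mm; two-sided alpha 0.033; power 90%; allocation 1:1; 190 per arm. Normal approximation and complete data throughout.

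**1. The plan's sample sizes.** n per arm = 2 × (SD/difference)² × (z for 1−alpha/2 + z for power)².

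- SF-36 at 0.033: 2 × 3² × (2.132 + 1.282)² = 209.8, so 210 (211 with the t distribution). The stated 190 is not reproduced.
- SF-36 at 0.05: 18 × (1.960 + 1.282)² = 189.1, so 190. This is the stated figure.
- Pain at 0.033: 2 × 2² × (2.132 + 1.282)² = 93.2, so 94 against 92 stated. At 92 the power is 89.6%, so this discrepancy is negligible.

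**2. SF-36 power at 190 per arm.** The expected z statistic is 4 / (12 × √(2/190)) = 3.249.

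- alpha 0.05: Φ(3.249 − 1.960) = 90.1%
- alpha 0.033: Φ(3.249 − 2.132) = 86.8% (86.6% by t)
- alpha 0.025: Φ(3.249 − 2.241) = 84.3%

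The Abstract gives 400 participants. With 200 complete cases per arm, power at 0.033 is 88.5%, still short of 90%.

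**3. Overall error of two tests at 0.033, p-value only.** Independent: 1 − (1 − 0.033)² = 0.0649. Upper bound: 0.033 + 0.033 = 0.066. From the bivariate normal distribution:

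| Correlation of test statistics | Overall error |
|---|---|
| 0 | 6.5% |
| 0.3 | 6.4% |
| 0.5 | 6.1% |
| 0.7 | 5.6% |
| 0.8 | 5.2% |
| about 0.85 | 5.0% |

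**4. Holm at overall 5%, 190 per arm.** The smaller p-value is tested at 0.025; if it passes, the other is tested at 0.05. The overall error is at most 5% at any correlation (simulated 4.0% to 5.0% over correlations 0 to 0.8).

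With independent outcomes, SF-36 power = P(p ≤ 0.025) + P(0.025 < p ≤ 0.05) × P(pain p ≤ 0.025).

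- Pain effect 10 mm: pain passes 0.025 with probability 0.9958, so 0.8432 + (0.9013 − 0.8432) × 0.9958 = 90.1%. Simulation gives 90.1% to 90.2% for correlations 0 to 0.8.
- Pain effect 5 mm: 87.7% if independent, falling to 85.1% at correlation 0.8.
- No pain effect: 0.8432 + 0.0581 × 0.025, about 84.5%.

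Holm matches the 86.8% of the fixed rule when pain passes 0.025 with probability (0.8680 − 0.8432) / 0.0581, about 43%. Pain power under Holm with the planned effects is 99.6% to 99.8%, against 99.7% under fixed 0.033.

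**The case against.** **No 5% target is stated.** This stands. The article openly gives 3.3% per outcome, with a citation, and uses 5% only for secondary outcomes. A reader might infer that it falsely claims 5% control, but the strengths section says only that several measures together limit random error. The criticism is that the rule does not reach the usual level and that no other level is declared.

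**The Bayes factor threshold may make the rule stricter.** This also stands, and it is the strongest point. Assume that the Bayes factor is the likelihood ratio of no effect to the planned effect at 190 per arm. A value below 0.1 then needs z > 3.249/2 + ln(10)/3.249 = 2.33 for the SF-36 and z > 4.873/2 + ln(10)/4.873 = 2.91 for pain. If both thresholds had to be crossed, the overall error for a benefit claim would be about 1.2% with independent outcomes. A reader might infer that the trial's false-positive rate is 6.5%. The article does not support that, because it leaves open how the two thresholds combine. For the same reason, the power figures above apply to the p-value rule only.

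**Holm is not simply the more powerful rule.** A reader might expect it to rescue borderline pairs. Two p-values of 0.04 fail under both rules, and two of 0.03 pass at fixed 0.033 but fail Holm. Nor does Holm repair the SF-36 calculation itself: it reaches 90% only by relying on the pain result.

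**The aim is not a decision rule.** The list of benefits in the Aim section also covers secondary outcomes, so it cannot define the primary family. The point does not need it: lowering the threshold for two outcomes already implies that either may succeed alone.

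**Conclusion.** The point holds on two counts.

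1. **SF-36 power is misstated.** With a difference of 4, SD 12 and two-sided alpha 0.033, 190 per arm gives 86.8%, not 90%. The stated sample size matches alpha 0.05. This follows from the article's own figures.
2. **The fixed threshold is a partial correction.** By p-value alone, the overall error is about 6.5% for independent outcomes and at most 6.6%. It exceeds 5% unless the test statistics correlate at about 0.85 or more, which the article nowhere assumes. The excess over 5% is at most 1.6 percentage points, so it is modest, and it depends on the p-value deciding alone.

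The figures assume complete data and treat the SD of a single pain score as valid for the pain analysis, although longitudinal data are to be analysed by area under the curve. The interim analysis is not included.

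**What to change.** Choose one of two options before unblinding.

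- **(a) Holm at overall two-sided 5%.** Test the smaller primary p-value at 0.025 and, if it passes, the other at 0.05. Report SF-36 power at 190 per arm as 90.1% if the 10 mm pain effect is true, about 88% at 5 mm with independent outcomes, and 84.5% with no pain effect. The cost is 86.8 − 84.5 = 2.3 percentage points of SF-36 power if pain truly does not differ.
- **(b) Keep 0.033.** State that the p-value rule alone allows an overall error of about 6.5%, and correct the SF-36 power at 190 per arm to about 87%. This costs no patients. Holding 90% at 0.033 would take 210 per arm, 20 more in each.

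Under either option, add one sentence saying whether the Bayes factor threshold of 0.1 must also be crossed for a primary claim. If it must, restate the overall error and the power for the joint rule. Apart from that recalculation, the change is a few sentences, and the planned analysis plan publication is a natural place for them.

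### The stated 90% power for SF-36 ignores the Bayes factor threshold and is not reached with or without it: about 82% if both significance thresholds must be crossed, 86.8% on p < 0.033 alone

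*Protocol article*

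**What the plan says.** The Statistical analyses section of the protocol article states: "We will assess if the thresholds for statistical significance and clinical significance are crossed using the five-point procedure". Within that procedure it names two numerical criteria. One is a p-"value threshold 0.033", adjusted for two primary outcomes. The other is a Bayes factor: "We will use a Bayes factor threshold for significance of 0.1 based on the prior anticipated intervention effect", with a pointer to the sample-size section. The same section says "We will perform two sided statistical tests". It does not say whether a primary outcome must cross both thresholds to count as significant, and it gives no formula for the Bayes factor.

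The sample-size section works from the type I error only. For SF-36 it takes a difference of 4 points and an SD of 12, and says "we accept a risk of type I error of 3.3% and a risk of type II error of 10" per cent, which leads to 190 per arm. For pain it takes 10 mm and an SD of 20 mm with the same error rates: "This results in a sample size of 92 patients in each arm of the trial". The larger figure, 2 × 190, is adopted for both outcomes.

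**The concern.** A Bayes factor measured against the planned effect is a second hurdle, and its height depends on the planned effect divided by its standard error. In a trial sized for about 90% power, a Bayes factor below 0.1 takes a larger test statistic than p < 0.033 does. The outcome with the most surplus sample size has the widest gap between the two hurdles. Here that is pain, which has about twice the number it needs.

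Two things are at stake. The type II error quoted for SF-36, the outcome that fixes the trial's size, may be wrong. And a result may pass one threshold and fail the other, while the article does not say what would then be concluded.

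**Working it through.** **Inputs (protocol article).** SF-36: difference 4, SD 12. Pain: difference 10 mm, SD 20 mm. Two-sided alpha 0.033, type II error 10%, 1:1 allocation, 190 per arm for both outcomes, Bayes factor threshold 0.1 at the planned effect.

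**Step 1: the stated sample sizes.** n per arm = 2 (SD/difference)² (z for alpha + z for power)², with z = 2.132 for two-sided 0.033 and 1.282 for 90% power.

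- SF-36: 2 × (12/4)² × (2.132 + 1.282)² = 18 × 11.65 = 209.8, so 210 per arm. The stated 190 is not reproduced.
- SF-36 with two-sided alpha 0.05: 18 × (1.960 + 1.282)² = 189.1, so 190. The stated number fits an unadjusted 5% test. One-sided 3.3% gives 176, so sidedness at 3.3% does not explain it.
- Pain: 2 × (20/10)² × 11.65 = 93.2, so 94, against a stated 92 (power 89.6% at 92). This agrees within rounding.

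**Step 2: SF-36 power on the p-value alone.** Standard error = 12 × √(2/190) = 1.231. Planned effect in standard-error units, θ = 4/1.231 = 3.249. Power = Φ(3.249 − 2.132) = Φ(1.117) = 86.8%.

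**Step 3: what the Bayes factor threshold demands.** Taking BF as the likelihood under no effect over the likelihood under the planned effect, BF = exp(−θz + θ²/2). So BF < 0.1 requires z > θ/2 + ln(10)/θ.

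| | SF-36 | Pain |
|---|---|---|
| Standard error, 190 per arm | 1.231 | 2.052 mm |
| θ | 3.249 | 4.873 |
| z needed for p < 0.033 | 2.132 | 2.132 |
| z needed for BF < 0.1 | 1.624 + 0.709 = 2.333 | 2.437 + 0.473 = 2.909 |
| Equivalent two-sided p | 0.0196 | 0.0036 |
| Power, p < 0.033 alone | 86.8% | 99.7% |
| Power, both thresholds | Φ(0.916) = 82.0% | Φ(1.964) = 97.5% |
| Observed difference for p < 0.033 | 2.62 | 4.37 mm |
| Observed difference for BF < 0.1 | 2.87 | 5.97 mm |
| BF at exactly p = 0.033 | 0.19 | 4.4 |

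In the direction of benefit, any result that crosses the Bayes factor threshold also crosses the p-value threshold. A rule requiring both therefore has the power of the Bayes factor rule, and a rule requiring either has the power of the p-value rule. Only two SF-36 figures are possible, 82.0% and 86.8%.

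**Step 4: splitting the SF-36 shortfall.** 90.0 − 86.8 = 3.2 points come from the sample size not matching alpha 3.3%. 86.8 − 82.0 = 4.8 points come from the Bayes factor.

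**Step 5: sensitivity.** With 200 per arm (the 400 women in the abstract), SF-36 θ is 3.333. Joint power is 83.5%, and p < 0.033 alone gives Φ(3.333 − 2.132) = 88.5%. Two other priors scaled to the planned effect raise the SF-36 hurdle further. A symmetric two-point alternative needs z > 2.547 (power 75.9%), and a normal prior with SD equal to the planned effect needs z > 2.779 (68.1%). The likelihood ratio against the planned effect is the most favourable to the trial of the three.

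**The case against.** The strongest reply is that the joint rule is an inference. The article lists the two thresholds inside a cited procedure and defers detail to a separately published analysis plan. Either source may say how the thresholds combine. That stands: a reader might infer that the article requires both to be crossed, but it does not say so. The 82% is therefore conditional. The power shortfall itself is not, because the p-value reading also falls short of 90%.

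A reader might also blame the Bayes factor for the whole drop from 90% to 82%. Step 4 does not support that: about 3 of the 8 points are already lost in the sample-size calculation.

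A third tempting reading is that the two thresholds contradict each other for pain. They do not. A stricter second criterion is no contradiction, and pain power stays at 97.5% under the joint rule. The discordant ranges (4.4 to 6.0 mm, and 2.6 to 2.9 points) also lie below the trial's own minimal relevant differences of 10 mm and 4 points. A Bayes factor that withholds support there adds information, and removing it from the decision would be a preference. It would also leave the 90% figure wrong.

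The millimetre limits need a caveat. Pain is measured at several times, and longitudinal data are to be analysed as an area under the curve, whereas the 20 mm SD is for a single score. The limits do not carry over directly.

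Finally, adjustment for the stratification variables could reduce the residual SD. To recover 90% at alpha 3.3% with 190 per arm, it would have to fall to about 12 × √(190/210) = 11.4. The sample-size section claims no such gain.

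**Conclusion.** The point holds in this form: the article sets two thresholds for significance, bases its power on one of them, and does not deliver the stated SF-36 power under either reading. At 190 per arm the power is about 82% if both thresholds must be crossed and 86.8% if the p-value alone decides, against the stated 90%. The section on trial strengths presents the sample size as adjusted for two primary outcomes, but the SF-36 figure corresponds to an unadjusted 5%.

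For pain the power is ample. What remains is an undeclared rule for discordant results, with p between 0.0036 and 0.033. At p = 0.033 the Bayes factor would be 4.4, favouring no effect.

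These figures assume a point alternative at the planned difference, normal approximations, the planned SDs, no missing outcomes and no gain from covariate adjustment. The 86.8% does not depend on how the Bayes factor is defined.

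**What to change.** State in Statistical analyses whether both thresholds must be crossed to declare a primary outcome significant or whether the p-value alone decides, and give the Bayes factor formula and its alternative. Then restate SF-36 power at 190 per arm in the sample-size section and the abstract: about 82% if both are required, about 87% if the p-value alone decides. For reference, 90% would take 210 per arm on the p-value alone and about 258 under the joint rule (the smallest n with θ − z ≥ 1.282, using the formulas above).

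The change is a few sentences and needs no new data. The price is a less favourable stated power for the outcome that determines the sample size.

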#### Interim analyses and early stopping

After collection of data from 100 patients, an independent safety and data monitoring committee will perform the first interim analysis. This committee will thereafter advise the steering committee and have the responsibility of monitoring whether the trial should be stopped early or continued until the sample size has been reached.

### Sample size calculation and power estimation

Because our trial is designed with two primary outcomes, our sample size calculation will be based on a type 1 error of 3.3% [15].

#### Postoperative pain

We use a 100 mm VAS-score to assess pain. We consider 10 mm as the minimal relevant difference with a standard deviation of 20 mm and we accept a risk of type I error of 3,3% and a risk of type II error of 10%. This results in a sample size of 92 patients in each arm of the trial.

#### SF 36 quality of life

We consider 4 points on the SF 36 quality of life as the minimal relevant difference with a standard deviation of 12 points and we accept a risk of type I error of 3.3% and a risk of type II error of 10%. This results in a sample size of 190 patients in each arm of the trial.

To be able to assess both of the co-primary outcomes, we therefore chose 2 × 190 participants as our necessary sample size.

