**Methods/design:**

The design is a randomised multicentre clinical trial. Participants will be 400 women referred for laparoscopic hysterectomy for benign indications. Patients will be randomized to 3-dimensional or conventional laparoscopic hysterectomy. Operative procedures will follow the same principles and the same standard whether the surgeon’s vision is 3-dimensional or conventional laparoscopy. Primary outcomes will be the impact of surgery on quality of life, assessed by the SF 36 questionnaire, and postoperative pain, assessed by a Visual Analogue scale for pain measurement. With a standard deviation of 12 points on SF 36 questionnaire, a risk of type I error of 3.3% and a risk of type II error of 10% a sample size of 190 patients in each arm of the trial is needed. Secondarily, we will investigate operative time, time to return to work, length of hospital stay, and - and postoperative complications.

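### The stated SF-36 inputs (difference 4, SD 12, two-sided 3.3%, 90% power) need 210 to 211 women per arm, not 190; 190 per arm gives about 87% power

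*Protocol article*

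**What the plan says.** The section Sample size calculation and power estimation explains that, because there are two primary outcomes, "our sample size calculation will be based on a type 1 error of 3.3" per cent. The subsection SF 36 quality of life takes 4 points as the minimal relevant difference and 12 points as the standard deviation. It repeats the error rates ("we accept a risk of type I error of 3.3% and a risk of type II error of 10" per cent) and concludes: "This results in a sample size of 190 patients in each arm of the trial". It then describes 2 × 190 "participants as our necessary sample size". The Postoperative pain subsection needs only 92 per arm, so SF-36 alone determines the size.

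The abstract (Methods/design) makes the same link, for each of the two groups: "a risk of type I error of 3.3% and a risk of type II error of 10% a sample size of 190 patients". The same paragraph says: "Participants will be 400 women referred for laparoscopic hysterectomy for benign indications".

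Statistical analyses settles the two remaining inputs. On sidedness: "We will perform two sided statistical tests". On the significance level, thresholds are adjusted for the "number of primary outcomes (*P*-value threshold 0.033"). Randomization gives a 1:1 allocation.

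**The concern.** The article gives every input to a standard two-sample calculation, and the stated result does not follow from them. The figure is not peripheral. It sets the size of the trial, and Trial strengths and limitations counts a sample size adjusted for two primary outcomes among the trial's strengths. If the adjustment did not reach the calculation that sets the size, the 10% type II error for SF-36 is not delivered. A reader of a null SF-36 result would then credit the trial with more power than it had.

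**Working it through.** **Inputs.** Difference d = 4 and SD s = 12 (SF 36 quality of life); alpha = 0.033 (same subsection, and Statistical analyses); two-sided tests (Statistical analyses); power 0.90; 1:1 allocation (Randomization).

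**Formula.** n per arm = 2 × [(z(1 − alpha/2) + z(0.90)) × s/d]², with s/d = 3 and z(0.90) = 1.282.

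**Trying to reproduce 190.**

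| Alpha | n per arm, normal | n per arm, t-test |
|---|---|---|
| 0.033 two-sided | 2 × [(2.132 + 1.282) × 3]² = 209.8, so 210 | 210.9, so 211 |
| 0.033 one-sided | 176 | 176.1 |
| 0.05 two-sided | 2 × [(1.960 + 1.282) × 3]² = 189.1, so 190 | 190.1 |

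Neither version at 3.3% gives 190. The two-sided 5% calculation does (one-sided 2.5% is the same calculation).

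**Power actually available at two-sided 0.033.** Power ≈ Φ[(d/s) × √(n/2) − 2.132].

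- n = 190: (1/3) × √95 = 3.249; 3.249 − 2.132 = 1.117; power 86.8% (t-test 86.6%). Type II error is about 13%.
- n = 200: (1/3) × √100 = 3.333; 3.333 − 2.132 = 1.201; power 88.5% (t-test 88.3%).
- For comparison, n = 190 at two-sided 0.05: 90.1% (t-test 90.0%).

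**Distance from the target.** 90% power needs 2 × 210 = 420 (normal) or 2 × 211 = 422 (t-test) evaluable women, which is 40 to 42 more than 380. Put differently, 190 per arm would be right at 3.3% if the SD were 4 × √95 / 3.414 = 11.4, or if the difference were 12 × 3.414 / √95 = 4.2.

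**Which alpha lies behind the other figures?**

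- Pain (difference 10 mm, SD 20 mm): 2 × [3.414 × 2]² = 93.2, so 94 per arm at 0.033, against 85 at 0.05. The stated 92 is close to the 3.3% answer.
- Length of stay (8 h, SD 25 h, 190 per arm): 83.8% at 0.033 and 87.7% at 0.05. The article states 84% and labels it 5%.
- Operative time (11 min, SD 36 min, 190 per arm): 80.1% at 0.033 and 84.6% at 0.05. The article states 81% and labels it 5%.

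So pain agrees with its label, SF-36 fits 5% although labelled 3.3%, and these two secondary powers lie nearer to 3.3% although labelled 5%. This pattern is consistent with the two levels having been mixed up between calculations.

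**The case against.** The strongest reply is that the loss is small. About 3 points of power is equivalent to an SD of 11.4 instead of 12, which is well within the uncertainty of any planning SD. The threshold of 0.033 still applies at analysis, so the type I error is not inflated. The other primary outcome, pain, has over 99% power at 190 per arm. All of this stands and limits how much weight the point can bear. It does not make the stated figure right: the article specifies the SD and both error rates, and they do not give 190.

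Several stronger readings are tempting but not supported:

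- *That the calculation was run at 5%.* The article never says so. The match is exact and the neighbouring figures fit the idea, but it remains an inference.
- *That 400 contradicts 380.* The abstract gives 400 participants and 190 needed per arm in one paragraph, and the body calls 2 × 190 the necessary size. An enrolment figure about 5% above the necessary one (20/380 = 5.3%) can be read as a recruitment margin. The article does not explain it, so it calls for a clarification.
- *That no loss to follow-up is allowed for.* If 400 is such a margin, loss is allowed for. No attrition rate is stated, and a fuller protocol may contain one.
- *That the rule for adjusting significance thresholds to the number randomised has no fixed reference.* The body names 2 × 190 as the necessary size, which is usable, and the details are deferred to an analysis plan that is not shown.

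**Conclusion.** The point holds as a numerical error in a stated design property. On the article's own inputs, SF-36 needs 210 to 211 women per arm for 90% power. With 190 evaluable per arm the power is about 87%, and with 200 it is about 88%, so neither total in the article delivers the stated 10% type II error. If 400 are randomised and 5% are lost (an assumed rate), 400 × 0.95 / 2 = 190 per arm remain and power is again about 87%.

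The conclusion assumes an unadjusted two-sample comparison, which is how the calculation is presented. A reader might infer that adjusting for baseline SF-36 would restore 90% without further change. That depends on a baseline correlation that the documents do not give: with 190 evaluable per arm, 0.30 gives 89.7%, about 0.32 is needed, and any loss raises that requirement. It cannot be relied on to rescue the stated figure.

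The consequence is confined to the power statement for one primary outcome. Neither the validity of the tests nor the adequacy of the pain calculation is in doubt.

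**What to change.** In the abstract (Methods/design) and in SF 36 quality of life, replace the statement that 190 per arm follows from 3.3% and 10%. Suggested wording: *With a difference of 4 points, an SD of 12 and a two-sided type I error of 3.3%, 190 evaluable women per arm give about 87% power; 90% power would require 210 to 211 per arm.*

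Add one sentence saying how the abstract's 400 relates to the necessary 2 × 190, for example that it is a margin for loss, if that was the intention.

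The cost is a correction of text and a slightly less favourable stated power. No additional patients are needed and the analysis does not change.
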